## Abstract

**Background:**

Childhood Apraxia of Speech is an impairment of speech motor planning that manifests as difficulty producing the sounds (articulation) and melody (prosody) of speech. These difficulties may persist through life and are detrimental to academic, social, and vocational development. A number of published single subject and case series studies of speech treatments are available. There are currently no randomised control trials or other well designed group trials available to guide clinical practice.

**Methods/Design:**

A parallel group, fixed size randomised control trial will be conducted in Sydney, Australia to determine the efficacy of two treatments for Childhood Apraxia of Speech: 1) Rapid Syllable Transition Treatment and the 2) Nuffield Dyspraxia Programme – Third edition. Eligible children will be English speaking, aged 4–12 years with a diagnosis of suspected CAS, normal or adjusted hearing and vision, and no comprehension difficulties or other developmental diagnoses. At least 20 children will be randomised to receive one of the two treatments in parallel. Treatments will be delivered by trained and supervised speech pathology clinicians using operationalised manuals. Treatment will be administered in 1-hour sessions, 4 times per week for 3 weeks. The primary outcomes are speech sound and prosodic accuracy on a customised 292 item probe and the Diagnostic Evaluation of Articulation and Phonology inconsistency subtest administered prior to treatment and 1 week, 1 month and 4 months post-treatment. All post assessments will be completed by blinded assessors. Our hypotheses are: 1) treatment effects at 1 week post will be similar for both treatments, 2) maintenance of treatment effects at 1 and 4 months post will be greater for Rapid Syllable Transition Treatment than Nuffield Dyspraxia Programme treatment, and 3) generalisation of treatment effects to untrained related speech behaviours will be greater for Rapid Syllable Transition Treatment than Nuffield Dyspraxia Programme treatment. This protocol was approved by the Human Research Ethics Committee, University of Sydney (#12924).

**Discussion:**

This will be the first randomised control trial to test treatment for CAS. It will be valuable for clinical decision-making and providing evidence-based services for children with CAS.

**Trial Registration:**

Australian New Zealand Clinical Trials Registry: ACTRN12612000744853

## Background

To date the consensus in the literature is that Childhood Apraxia of Speech (CAS) is a disorder of speech motor programming and planning with genetic, neurologic, or idiopathic causes [1-4]. Children with the disorder have significant speech impairments due to an inability to control placement and timing of lip, tongue and vocal movements. These impairments result in inconsistent productions of the same words, difficulty sequencing speech sounds together to form fluent words and sentences and impairments of the melody (i.e. prosody) of speech. The speech of these children is often unintelligible and the disability can persist throughout the lifespan, despite normal intelligence and comprehension of language [5,6]. The impaired development of speech has flow on effects, frequently disrupting development of reading, spelling and writing skills (e.g. learning letter-sound relationships for deciphering new words), social communication, and academic potential [6,7]. Adults with speech disorders (including persistent CAS) are known to have a lower socio-economic status than non-speech disordered peers, an increased incidence of depression and may select occupations that require little or no personal interaction despite normal intelligence [6,8,9]. Speech pathologists frequently report that children with CAS make slow progress in treatment and show deterioration or loss of skills once treatment stops [10,11]. It is unclear if this is due to the child’s impaired motor learning or to a lack of evidence to inform effective treatment [10,12,13]. Due to CAS’s characteristics and associated risk factors, the ultimate aim of treatment must be long term maintenance of learned skills and generalisation of treatment effects to improvement across untrained but related speech skills and speaking contexts.

There are few rigorous treatment studies published for CAS currently and no randomised control trials to date [1,14]. The best evidence available consists of single case experimental designs and case series for a range of different treatments across different age ranges with samples sizes no greater than twelve (e.g. [15]). Published speech-focussed treatments with some replicated evidence include the Rapid Syllable Transition Treatment (ReST) [12,16], Dynamic Temporal and Tactile Cueing (DTTC) [17,18] and the Nuffield Dyspraxia Programme - Third edition (NDP3) [19-21]. Replicated evidence also exists for pre-reading and spelling interventions [15,22,23] and alternative or augmentative communication methods [24-28] that work on communication skills. These methods are the best poised to be utilised clinically at present and also to be included in any controlled trial. Other published evidence includes studies on melodic-intonation therapy (speech melody) therapy [29] and speech rate control [30]. Recently, intervention studies have included combined approaches such as a combined stimulability and core vocabulary approach [31] and a combined melodic intonation therapy and touch-cue method [32]; the PROMPT approach [33] and technological interventions providing graphic displays of tongue movements during speech such as electropalatography [20,34]. Moreover there are many published commercial programmes for CAS, which have no published evidence to date. Examples include the Kaufman Speech Praxis Treatment Kits [35-37] and the Easy Does It For Apraxia series [38,39]. It is relevant to note that children with CAS have different needs as their skills change with maturation and therapy and so it is plausible that multiple treatments will be effective but for different symptoms, severities and ages. In summary, while consumers and clinicians have a range of potential intervention programmes available, few have been experimentally tested and none have been experimentally compared. A Cochrane review on the topic states “there is a critical lack of well controlled treatment studies addressing treatment efficacy for CAS” [14] pg 2.

### Nuffield Dyspraxia Programme – Third edition (NDP3)

At time of writing, the Nuffield Dyspraxia Programme is in its third edition and has been utilised in clinical practices in Australia and the United Kingdom for approximately 30 years [40,41]. The comprehensive treatment package includes its own assessment as well as a list of over 500 words to be targeted in therapy, and corresponding therapy stimulus pictures. The theoretical basis of the programme is that motor learning is complex and hierarchical; one needs to perform frequent and systematic practice to master foundation levels before progressing to harder, more complex speech patterns. Here mastery is defined as fluent, automatic and independent production of targeted speech behaviours. To date, a total of five empirical case studies have demonstrated positive outcomes for this treatment alone [19,21], or in conjunction with electropalatography therapy [20]. Given these results and the programme’s broad dissemination, testing the programme in a randomised control trial is appropriate.

### Rapid Syllable Transition Treatment (ReST)

The ReST treatment is a more recently conceived and tested treatment approach [12]. The programme is grounded in theory of motor control and learning and is informed by an extensive motor learning literature [42]. The ReST treatment applies Principles of Motor Learning [43] with an aim to maximise long-term maintenance and generalisation of treated speech skills in children with CAS. ReST involves intensive practice in producing multisyllabic pseudo-words (e.g. toobiger) to improve the accuracy of speech sounds, the ability to transition rapidly and fluently from one sound/syllable to the next, and control of the melody in the form of relative emphasis, or stress, placed on each syllable within a word. Pseudo-words are used to mimic novel word learning and this allows children to develop and practice new speech patterns without interference from existing erroneous speech patterns. There is published evidence that the effects of speech treatment using phonotactically permissible pseudo-words (non-words) generalise to improved production of real words of similar or easier composition and complexity [44]. ReST involves two components within each treatment session. The first is a Pre-Practice (or training) Component where the stimuli are taught with cues to shape accurate production and immediate, specific feedback is given after each production. This is followed by a longer Practice Component incorporating those Principles of Motor Learning that have been shown to facilitate long-term learning and generalisation of skill. For example, “right/wrong” (i.e. Knowledge of Results or KR) feedback is provided by the clinician, fading from high frequency to low frequency over the session (i.e. provided on a total 50% of responses) and this KR feedback is delayed with a silent interval between response and feedback to encourage self-evaluation. Two published case series involving a total of ten children [12,16] indicate strong clinical effects for ReST treatment, motivating further study in a phase three trial.

Based on these foundational studies, we are well poised to conduct a larger scale clinical trial of ReST treatment against NDP3. Our hypotheses for this planned randomised control trial are: 1) treatment gains from pre-treatment to 1 week post-treatment will be similar for both treatments, 2) ReST treatment will result in greater maintenance of treatment effects at 1 and 4 months post-treatment than NDP3 treatment, and 3) ReST treatment will result in greater generalisation of treatment effects to untrained but related speech behaviours at 1 week, 1 month and 4 months post-treatment than NDP3 treatment.

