## Methods and design

A parallel group, fixed size randomised control trial will be conducted in Sydney, Australia to determine the comparative efficacy of two treatments for Childhood Apraxia of Speech: the Rapid Syllable Transition Treatment (ReST) and the Nuffield Dyspraxia Programme – Third edition (NDP3). This protocol has been approved by the Human Research Ethics Committee of the University of Sydney (approval number 12924).

A power calculation has been used to determine the number of participants to be recruited. Previous pre and post treatment data from within-subject ReST studies (e.g. [12,16]) for a total number of 14 participants demonstrated statistically significant differences for 12 of the 14 participants and large effect sizes (Cohen’s d = 1.36). Based on this, the estimated sample size to detect a reliable treatment effect (alpha level 0.05, beta level 80%) is 6 per group for this RCT. We have no estimates for the NDP3 due to lack of published effect sizes or data to enable calculation of an effect size. On this basis we propose 10 per group to allow for attrition and to accommodate the higher heterogeneity with a between-subjects design.

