#### Data analysis

Clinical effect sizes will be reported using Cohen’s d. A series of repeated measures ANOVA with between subject factor of treatment (NDP3, ReST) and within subject factor of time (pre-, 1 week post-, 1 month post-, and 4 months post-treatment) will be used to determine the relative efficacy of the two treatments as measured by the 292-item experimental probe. Separate analyses will be run for treated stimuli, to document treatment and maintenance effects, and untreated stimuli, to document generalisation of treatment effects and their maintenance. Additional repeated measures ANOVA (2 groups x 4 time points) will be run for the DEAP Inconsistency subtest [49], GFTA-2 [58] and the Test of Polysyllables [50,51]. If there is any attrition, an intention-to-treat analysis will be conducted.

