## Discussion

### Potential significance

This will be the first randomised control trial to test any treatment for CAS [14]. It is predicted that this will be valuable for clinical decision making and ultimately for providing evidence-based and timely services for children with CAS which may improve access to services and reduce the burden of the disorder. Potentially both treatments will be shown efficacious to some degree or for specific behaviours, which offers two evidence-based options tested at a gold standard level. If the treatments are successful, further work in ensuring time-efficient translation into practice can be pursued in effectiveness studies, knowing the treatments are efficacious and such work is warranted. Examples of this may include computer-based delivery of treatment to promote home practice and achieve treatment intensity with fewer face-to-face clinician-directed sessions.

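### Hypothesis 1 predicts similar 1-week gains, but the only stated test looks for a difference in 20 to 30 children; it needs an estimation rule, and the efficacy wording should stay comparative

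*Protocol article*

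**What the plan says.** Hypothesis 1 closes the Background (under Rapid Syllable Transition Treatment) and is repeated in the Abstract: "treatment gains from pre-treatment to 1 week post-treatment will be similar for both treatments". Hypotheses 2 and 3 predict that ReST will do better on maintenance and on generalisation.

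Data analysis gives one inferential method: "A series of repeated measures ANOVA with between subject factor of treatment (NDP3, ReST) and within subject factor of time", at four time points (pre-treatment, 1 week, 1 month, 4 months), run separately for treated and untreated stimuli. It "will be used to determine the relative efficacy of the two treatments as measured by the 292-item experimental probe". The section also says "Clinical effect sizes will be reported using Cohen’s d". It gives no margin, and no rule for deciding when gains count as similar.

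Methods and design sizes the trial to find an effect: "the estimated sample size to detect a reliable treatment effect (alpha level 0.05, beta level 80%) is 6 per group for this RCT". This is raised to 10 per group, and Intervention delivery and dosage allows 20 to 30 children in total.

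The aim is worded in two ways. The Abstract speaks of the efficacy of the two treatments, while Methods and design speaks of their comparative efficacy. Potential significance adds: "Potentially both treatments will be shown efficacious to some degree or for specific behaviours". It then describes later effectiveness work as starting from treatments already known to be efficacious.

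**The concern.** Hypothesis 1 states similarity, but the test attached to it can only reject equality. With no other rule, the one result that could appear to favour Hypothesis 1 is a non-significant p-value, and a trial of this size often produces that even when the treatments differ substantially.

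A second, separate issue is the absence of an untreated arm. Within-arm improvement then mixes treatment effect with maturation and repeated exposure to the same probe. By 4 months it also includes usual speech pathology services, which by then have resumed for up to 3 months (Outcome assessments and measures). Comparing the arms handles what they share; change within an arm does not.

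At stake are two statements that clinicians could take from what the article calls the first randomised trial in this disorder: that the treatments work equally well in the short term, and that both are proven.

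**Working it through.** **1. The plan's own figure.** Inputs from Methods and design: d = 1.36 (pre-post, within-subject, ReST only), alpha 0.05, and 80%, read as power. For NDP3: "We have no estimates for the NDP3 due to lack of published effect sizes or data".
- Paired t-test, two-sided: n = 6.4, so 7 (power at n = 6 is 75.9%). The stated 6 is close to this.
- Two-sample t-test, two-sided: n = 9.55, so 10 per group.

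Either way, the calculation sizes the trial for detecting an effect. It does not address showing that two arms are alike.

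**2. What the ANOVA can say about Hypothesis 1.** Suppose Hypotheses 1 and 2 are both true: equal gains at 1 week, divergence later. The group-by-time interaction over four time points is then non-zero although Hypothesis 1 holds. Conversely, a non-significant interaction does not show equal gains at 1 week. The group main effect averages over all four times, including baseline. Neither term is the pre to 1-week contrast.

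**3. Precision without adjustment** (units: SD of the analysed score).
Half-width of the 95% CI = t(0.975, 2n−2) × √(2/n).
- n = 10: 2.101 × 0.447 = 0.94
- n = 15: 2.048 × 0.365 = 0.75

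Probability that a true 0.8 SD difference is non-significant (noncentral t, two-sided 0.05): 1 − 0.395 = 60% at n = 10, and 1 − 0.562 = 44% at n = 15.

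**4. Precision with baseline adjustment** (units: outcome SD). The article gives no pre-post correlation ρ, so 0.5 to 0.8 is assumed. Half-width = t(0.975, 2n−3) × √(2/n) × √(1−ρ²).
- n = 10, ρ = 0.5: 2.110 × 0.447 × 0.866 = 0.82
- n = 10, ρ = 0.8: 2.110 × 0.447 × 0.600 = 0.57
- n = 15, ρ = 0.5: 2.052 × 0.365 × 0.866 = 0.65
- n = 15, ρ = 0.8: 2.052 × 0.365 × 0.600 = 0.45

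A true 0.8 SD difference is then missed about 50% to 20% of the time at n = 10, and 32% to 6% at n = 15.

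**5. Chance of showing similarity when the treatments are identical.** Two one-sided tests (TOST) at 0.05, equivalent to the 90% CI lying inside ± the margin; by simulation. The article gives no margin; 0.5 and 0.8 SD are assumed to show the range.

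| | Margin 0.5 SD | Margin 0.8 SD |
|---|---|---|
| n = 10, unadjusted | 0.1% | 12% |
| n = 10, adjusted, ρ 0.5 to 0.8 | about 1% to 16% | 28% to just under 78% |
| n = 15, unadjusted | 0.6% | 38% |
| n = 15, adjusted, ρ 0.5 to 0.8 | 4% to 44% | 59% to 94% |

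**6. The efficacy wording, side by side.** Methods and design (comparative efficacy) and Data analysis (relative efficacy) match a two-active-arm design. The Abstract aim and Potential significance go further. The untreated stimuli do not fill the gap: Data analysis uses them to measure generalisation, and Hypothesis 3 concerns treatment effects carrying over to such items, so they are not a no-treatment condition.

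**The case against.** A reader might infer that the authors plan to declare equivalence from a non-significant p-value. The article does not say so. It never uses the word equivalence, and *similar* may be only an expectation set beside two superiority hypotheses. That objection stands: the misreading is a risk the plan leaves open, not something it prescribes.

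It is also fair that Cohen's d is planned, so an effect estimate will exist, and that a margin or interval could sit in a fuller document. But a point estimate without an interval or rule does not test similarity. The article itself already pairs this hypothesis with a difference test and a sample size chosen for detection.

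The unadjusted figures are the pessimistic end. With adjustment and a high pre-post correlation, a wide margin becomes attainable, especially at 15 per arm. So the stronger reading, that this trial could never support similarity, is not established either.

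On efficacy, the relative-efficacy wording in Data analysis is correct, and the Discussion sentence is hedged. Having two active arms is a legitimate design choice. A reader might add regression to the mean on the primary probe. The documents give weak grounds for this: Eligibility assessment selects on expert diagnosis and a checklist, and the probe is a separate baseline measure. It is not relied on here.

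**Conclusion.** The point holds as a mismatch between Hypothesis 1 and its analysis: following the plan as written cannot support a claim of similar gains at 1 week. Unadjusted, differences up to about 0.94 SD (10 per arm) or 0.75 SD (15 per arm) on either side of the estimate stay compatible with the data. With adjustment at 10 per arm this is about 0.82 to 0.57 outcome SD, assuming a correlation of 0.5 to 0.8. Under the same assumption, similarity is very hard to show at 10 per arm for a 0.5 SD margin (about 1% to 16%) and possible but uncertain for 0.8 SD (28% to just under 78%). The figures assume roughly normal scores, equal arms, equal variances and no attrition; the margins and correlations are assumptions, not values from the article.

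The efficacy point is narrower. It concerns the Abstract aim and the two statements in Potential significance, not the analysis itself.

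**What to change.** 1. Make the Hypothesis 1 analysis the baseline-adjusted difference between arms at 1 week on the treated stimuli, reported with 90% and 95% CIs.
2. State that a non-significant group or interaction effect will not be read as similarity.
3. Fix and justify a margin before unblinding. Use *similar* only if the 90% CI lies wholly inside it; otherwise report the result as inconclusive. If no margin can be justified, present Hypothesis 1 as estimation only and make no claim of similarity.
4. Align the Abstract aim and both efficacy statements in Potential significance with the comparative wording in Methods and design and Data analysis.

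The cost is one margin, some wording and a narrower permitted conclusion. No extra children, arm or assessment is needed.

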## Methods and design

A parallel group, fixed size randomised control trial will be conducted in Sydney, Australia to determine the comparative efficacy of two treatments for Childhood Apraxia of Speech: the Rapid Syllable Transition Treatment (ReST) and the Nuffield Dyspraxia Programme – Third edition (NDP3). This protocol has been approved by the Human Research Ethics Committee of the University of Sydney (approval number 12924).

A power calculation has been used to determine the number of participants to be recruited. Previous pre and post treatment data from within-subject ReST studies (e.g. [12,16]) for a total number of 14 participants demonstrated statistically significant differences for 12 of the 14 participants and large effect sizes (Cohen’s d = 1.36). Based on this, the estimated sample size to detect a reliable treatment effect (alpha level 0.05, beta level 80%) is 6 per group for this RCT. We have no estimates for the NDP3 due to lack of published effect sizes or data to enable calculation of an effect size. On this basis we propose 10 per group to allow for attrition and to accommodate the higher heterogeneity with a between-subjects design.

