### Intervention delivery and dosage

The two treatments will be conducted in parallel within three treatment blocks over school holiday time in Sydney, Australia, permitting a maximum of 10 participants per block to allow for recruitment of between 20 and 30 participants across 3 treatment blocks. Treatments will be delivered by trained and supervised speech pathology clinicians. Each child will be allocated one clinician for all treatment sessions. Clinicians will be blinded to hypotheses. The parents of children will not be informed of the name and strategies of the treatment their children are receiving until after data collection is completed to ensure no home practice will be attempted.

All participants, regardless of treatment condition, will receive the same amount of time in treatment with 1-hour sessions, four times a week for three weeks for a total of 12 treatment hours. All participants will complete between 100–120 production trials on treatment words per 1-hour session (i.e. a total of 1200 to 1440 responses during treatment), to match the practice intensity and session distribution of our pilot studies of ReST [12,16] and the current best evidence of treatment intensity for CAS [61]. For the NDP3 programme this will equate to approximately 30–40 trials during each 18 minute period for each goal. For the ReST programme, this will equate to 5–20 Pre-Practice trials and 100 practice trials.

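### The sample size rests on a within-child pre-post effect of ReST, so the stated 80% power does not apply to the ReST-versus-NDP3 comparison that the trial tests

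*Protocol article*

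**What the plan says.** Under Methods and design, the protocol article bases its effect size on "Previous pre and post treatment data from within-subject ReST studies", pooling 14 participants, and reports d = 1.36. From this it states that "the estimated sample size to detect a reliable treatment effect (alpha level 0.05, beta level 80%) is 6 per group for this RCT". It then concedes: "We have no estimates for the NDP3 due to lack of published effect sizes or data to enable calculation of an effect size". The planned size follows: "we propose 10 per group to allow for attrition and to accommodate the higher heterogeneity with a between-subjects design". It gives no dropout rate, variance inflation, between-treatment difference or power for the 10 per group.

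The Background sets three hypotheses: similar gains at 1 week (hypothesis 1), better maintenance with ReST at 1 and 4 months (hypothesis 2), and more generalisation with ReST (hypothesis 3). The Data analysis section tests them with a repeated measures ANOVA that has treatment as the between-subject factor and four time points.

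The Abstract commits to at least 20 children. Intervention delivery and dosage limits each block to 10 children "to allow for recruitment of between 20 and 30 participants across 3 treatment blocks", and Group allocation prepares participant numbers 1 to 30.

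**The concern.** A pre-post d for one treatment measures how far children move from their own baseline. It includes maturation, practice on the probe and anything else that changes over time. Hypotheses 2 and 3 need a different quantity, the difference between two active treatments, and the first does not estimate the second. Hypothesis 1 makes the gap plain. If both arms are expected to gain about equally at 1 week, a later between-arm difference as large as the whole ReST pre-post gain is a very optimistic target.

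At stake is how the result will be read. The power paragraph is the protocol's only statement of what the trial can detect. If about 20 children show no significant difference, a reader who relies on that paragraph could take the result as evidence that the treatments are alike, when the trial could miss a large difference.

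**Working it through.** **Inputs from the protocol.** d = 1.36 (within-child, ReST only), alpha 0.05, 80% read as power, 6 per group derived, 10 per group planned, up to 30 children in total (15 per group). The test, its sidedness and the standardiser of d are not stated. Two-sided is assumed unless noted.

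**1. Where 6 could come from.**
- *Paired t-test on one group, two-sided* (d taken as standardised by the SD of change). The noncentrality is d√n = 1.36 × √6 = 3.33 on 5 df, and power is 75.9%. The solution is n = 6.4, so 7 children (84.8%). One-sided, 5 are enough (80.0%).
- *Between-group factor of a repeated measures ANOVA*, f = 1.36/2 = 0.68, 4 time points, correlation ρ between times assumed. The noncentrality is f² × 2n × 4 / (1 + 3ρ). At 6 per group, power is 87% for ρ = 0.3, 82% for ρ = 0.4, 77% for ρ = 0.5 and 68% for ρ = 0.7. The required size is 6 per group for ρ = 0.3 or 0.4, 7 for 0.5 and 8 for 0.7.

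So 6 is close to a one-group paired calculation and can be recovered exactly from a repeated-measures calculation at modest correlations. The second route still uses 1.36 as a between-group difference. It also takes that difference as the same at all four times, including before treatment, where randomised groups should not differ.

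**2. The same d in a two-sided two-sample t-test at one time point.** The noncentrality is d√(n/2) on 2n − 2 df.

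| n per group | noncentrality | power |
|---|---|---|
| 6 | 1.36 × √3 = 2.36 | 56.6% |
| 8 | 1.36 × √4 = 2.72 | 71.6% |
| 9 | 1.36 × √4.5 = 2.88 | 77.3% |
| 10 | 1.36 × √5 = 3.04 | 82.0% |
| 15 | 1.36 × √7.5 = 3.72 | 94.9% |

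The solution for 80% is n = 9.55, so 10 per group. The normal approximation gives 2 × (1.960 + 0.842)² / 1.36² = 8.49, so 9. To keep 10 analysed per group, an assumed dropout of 10% needs 10/0.9 = 11.1, so 12 enrolled; 20% needs 10/0.8 = 12.5, so 13.

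**3. Tests that leave slack at d = 1.36.**
- One-sided two-sample t-test: 8 per group gives 82.6%.
- Two-sided with baseline adjustment, at an assumed correlation r between baseline and outcome. The effective d is 1.36/√(1 − r²), with one df fewer. At 8 per group, power is 83% for r = 0.5 and 94% for r = 0.7.
- The repeated-measures test of step 1: 8 per group gives 82% even at ρ = 0.7.

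**4. What the trial can detect.** The difference detectable with 80% power (two-sided, unadjusted, one time point) is 1.51 SD at 8 per group, 1.32 SD at 10 and 1.06 SD at 15. With baseline adjustment at an assumed r of 0.5 to 0.7, the figure at 10 per group is about 1.32 × √0.75 = 1.15 down to 1.32 × √0.51 = 0.95 SD.

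If the true difference were half the ReST pre-post effect (0.68, an assumption), the unadjusted test has 30% power at 10 per group and 44% at 15. For an assumed difference of 1.0 SD the figures are 56% and 75%.

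**The case against.** The authors do not offer 6 as enough. They disclose that no NDP3 estimate exists, recognise that a between-subjects design is more variable, and raise the number to 10. This stands as disclosure. It supplies no between-treatment difference and no power for the 10.

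A reader might infer three stronger points, none of which the document supports.

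- *That 6 is an arithmetic error.* The test and sidedness are not stated. The figure is near a paired calculation and follows from a repeated-measures between-group test at an assumed correlation of 0.3 to 0.4. What can be said is that 6 falls well short of 80% power on a two-sided two-sample t-test.
- *That 10 per group holds no allowance for attrition.* This is so only for a two-sided, unadjusted test at a single time point. One-sided, baseline-adjusted or repeated-measures tests leave some room at d = 1.36, and the protocol allows up to 30 children.
- *That the 14 participants contradict the ten children credited to the two case series in the ReST section.* The power paragraph cites those two series only as examples of its source studies, so ten within a pool of 14 is consistent.

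The beta label on the 80% is a slip that changes no number.

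**Conclusion.** The concern holds on its main point, which depends on neither sidedness nor rounding: a within-child effect of one treatment has been turned into a per-group number for a comparison of two treatments, so the stated 80% power does not apply to hypotheses 2 and 3.

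On the size of the problem, if 1.36 is granted as the between-group difference and the test is a two-sided, unadjusted t-test at one time point, 6 per group gives 57% power and 10 gives 82%, so the planned size is about the minimum. Other tests or fuller recruitment ease this. None of them makes 1.36 an estimate of the ReST-NDP3 difference. With 10 per group analysed, that t-test reaches 80% power only for a difference of about 1.3 SD. The correlations, dropout rates and alternative differences used above are assumptions, not figures from the protocol.

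**What to change.** In the power paragraph:

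1. Remove 6 per group as the basis for the RCT.
2. Say that the pre-post d of 1.36 describes change under ReST and does not estimate the ReST-NDP3 difference.
3. State what the planned size can detect, for example: *With 10 children per group analysed, the trial has 80% power (two-sided 0.05, single time point, unadjusted) for a between-treatment difference of about 1.3 SD; the figure is 1.5 SD if 8 per group remain and 1.06 SD at 15 per group. Smaller differences will be reported as estimates with 95% confidence intervals.*
4. Label the 80% as power instead of beta.

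This is a change of wording. It needs no extra children and no change to the design or analysis. The cost is that the stated power looks less favourable.
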